# The coagulation parameter fibrinogen is analyzed as efficacy variable.

\* Categorical analysis with 'Positive' and 'Negative'.

° Before CRF version 4.1, the parameter titled "Blood in urine".

For each numeric parameter, the baseline value will be determined as the latest value before or at Day 1. Then, values at Baseline and Day 8 as well as the absolute change will be given in a summary table by treatment group.

Moreover, a shift analysis will be presented for each numeric parameter. In this, the categorized change from Baseline to Day 8 will be displayed. Possible categories are 'Below the LLN', 'Within the normal range', and 'Above the ULN', according to the flag variable introduced in Section 4.3.

Categorical parameters will be presented in frequency tables by visit (Baseline, Day 8).

The number of patients with clinically relevant laboratory values will be given by parameter in a frequency table.

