#### **4.5 Early Termination Visit**

If a patient prematurely terminates the study, a complete final examination as detailed in Section 4.2 is to be performed at the time of withdrawal. Furthermore the blood sample for determination of the neutralizing anti-ancrod antibody should be taken on day 30 ( $\pm$  one week) if possible.

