#### **Coagulation**

Blood samples for coagulation (Fibrinogen according to Clauss, TT, PT and aPTT) will be drawn prior to study drug infusion (baseline value at screening), two days (Visit 2) and 8 days (Visit 5) after initiation of study drug. Coagulation parameters during screening are used for the determination of the duration of study drug infusion and will be assessed in the local laboratory. The following measurements will be performed in the selected laboratory (local or central) of the site.

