### 8.2.3 Special Assays or Procedures

The occurrence of neutralizing anti-ancrod antibodies will be determined in blood samples collected at screening, Day 8, and Day 30. Antibody titers will be quantified according to the method described by Vinazzer, 1973.

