#### 3.4.3. Safety Variables

Clinical safety assessments include:

- Adverse event reporting
- Change from Screening to Day 8 in general physical examination findings
- Change from Screening to Day 8 in otolaryngological examination findings
- Change from Screening to Day 8 in vital signs
- Change in laboratory parameters
- Occurrence of neutralizing anti-ancrod antibodies at Screening, Day 8, and Day 30.

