Data source for prior and concomitant medications are all findings being recorded in the CRF module "Concomitant Medication" located in the CRF for each study visit.
- A flag variable will be derived to indicate the status of laboratory values:  
*Conversions* to the standardized unit are marked in listings by a '&' sign.  
A value *below* the lower limit of the normal range (LLN) will be indicated by a '<' mark;  
a value *above* the upper limit of the normal range (ULN) will be indicated by a '>' mark.  
Normal ranges are available only for lab values provided by the central lab (as part of the transferred data) and will be used for flag derivation; for lab values from local laboratories as entered in the CRF no normal ranges are available.

- A flag variable will be derived indicating visits or *assessments being out of the scheduled time frame* by '#'. The following time frames will be used to identify out-of-range assessments:
  - Screening (Visit 1): Start time of visit is earlier than 36 hours before the start time of first study infusion
  - Visit 2, Day 2): Not on study Day 2
  - Visit 3 (Day 4): Not on study Day 4 or 5
  - Visit 4 (Day 6): Not on study Day 6 or 7, or the day before Visit 4 is a day with IMP dose
  - Visit 5 (Day 8): Not on study Day 7 to 9, or the day of Visit 5 is a day with IMP dose
  - Visit 6 (Day 30): Earlier than Day 23 or later than Day 37
  - Visit 7 (Day 90): Earlier than Day 83 or later than Day 97.Deviations from the visit schedule represent a protocol deviation and are reviewed at the BDRM to determine their consequence.

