## 10.3. Laboratory Data

Data on laboratory parameters are provided in the CRF or electronically by the central lab. They refer to blood coagulation, clinical chemistry, hematology, biomarkers, antibodies, and urinalysis; relevant for safety purposes are all except biomarkers. If a value is available twice (in the CRF and in the central lab data), both will be listed but only the CRF value will be used for statistical analysis.

All results of laboratory tests will be listed, including reference ranges (available only for central lab data) and possible details on conversion to the standardized units shown in below table. Unusual lab values are reviewed at the BDRM. Values recorded as lower or upper border only will be evaluated as the border (e.g. >140 as 140); however, if all values of a parameter are recorded as border value, the analysis will only be categorical.

The laboratory parameters will be displayed in the analysis in the order as shown in Table 2:

TABLE 2: LABORATORY PARAMETERS

| Group      | Parameter (standardized unit)        |
|------------|--------------------------------------|
| Hematology | Hemoglobin (g/dL)                    |
|            | Hematocrit (%)                       |
|            | Erythrocytes ( $10^6/\mu\text{L}$ )  |
|            | Leukocytes ( $10^3/\mu\text{L}$ )    |
|            | Thrombocytes ( $10^3/\mu\text{L}$ )  |
|            | Mean cell volume ( $\mu\text{m}^3$ ) |

| Group           | Parameter (standardized unit)         |
|-----------------|---------------------------------------|
|                 | ESR (mm/h)                            |
| Blood chemistry | Creatinine (μmol/L)                   |
|                 | GOT/ASAT (U/L)                        |
|                 | GPT/ALAT (U/L)                        |
|                 | Sodium (mmol/L)                       |
|                 | Potassium (mmol/L)                    |
|                 | Chloride (mmol/L)                     |
|                 | Glucose (mmol/L)                      |
|                 | Urea (mmol/L)                         |
|                 | Uric acid (μmol/L)                    |
|                 | Phosphorus (mmol/L)                   |
|                 | Total bilirubin (μmol/L)              |
|                 | Total protein (g/L)                   |
|                 | Albumin (g/L)                         |
|                 | LDH (U/L)                             |

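### SAP 10.3 gives Day 30 antibodies and Day 2 TT, PT and aPTT no by-visit summary, and its duplicate rule can select a value that the shift table cannot classify

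*Combined protocol and SAP*

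**What the plan says.** **Antibodies.** Protocol 8.2.3 states: "The occurrence of neutralizing anti-ancrod antibodies will be determined in blood samples collected at screening, Day 8, and Day 30". SAP 3.4.3 carries this over as a safety variable: "Occurrence of neutralizing anti-ancrod antibodies at Screening, Day 8, and Day 30". For patients who leave early, Protocol 4.5 makes a special request: "Furthermore the blood sample for determination of the neutralizing anti-ancrod antibody should be taken on day 30" (within a week either way, if possible). SAP Table 2 marks antibodies as categorical, positive or negative.

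**Coagulation times.** Protocol 4.2 draws TT, PT and aPTT together with fibrinogen on Day 2 and gives safety as the reason. Protocol 8.2.2 schedules them at screening, Visit 2 and Visit 5. The screening coagulation parameters "will be assessed in the local laboratory"; later samples go to the laboratory selected by the site, local or central.

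**Tables.** SAP 10.3 says of categorical results: "Categorical parameters will be presented in frequency tables by visit (Baseline, Day 8"), and names no other visit. For numeric results, "values at Baseline and Day 8 as well as the absolute change will be given in a summary table by treatment group". The shift table compares Baseline with Day 8. A further table (14.3.4.4) counts patients with clinically relevant values by parameter and sets no visit limit. All results are listed.

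**Duplicates and ranges.** When a result is in both the CRF and the central-laboratory file, "both will be listed but only the CRF value will be used for statistical analysis". SAP 4.3 takes normal ranges from the central data only and adds that "for lab values from local laboratories as entered in the CRF no normal ranges are available".

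**The concern.** The SAP names a safety variable at three time points and then writes a table rule that covers two of them. SAP section 2, which sets out departures from the protocol, does not mention this. The time point left out for antibodies is the late one, which the protocol tries to obtain even from patients who stop early. Any antibody that first appears after Day 8 would enter no planned rate by arm. For TT, PT and aPTT, the time point left out is the day after the infusion.

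The duplicate rule raises a second, smaller question. The shift table needs a normal range, ranges come only with central data, and the rule prefers the CRF. Where the CRF value is a local one, the plan passes over the result that it could classify.

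At stake is whether the report gives planned, by-arm figures for these results, or leaves them to be counted from listings or tabulated after unblinding.

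**Working it through.** The point rests on no sample size, power or alpha figure, so there is none to reproduce. The check sets the sampling schedule beside the planned tables.

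**Step 1: scheduled against tabulated.**

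| Result | Sampled (Protocol 4.2, 8.2.2, 8.2.3) | Visits in by-visit tables | Left out |
|---|---|---|---|
| Antibodies | Screening, Day 8, Day 30 | Baseline, Day 8 (Table 14.3.4.3) | Day 30 |
| TT, PT, aPTT | Screening, Day 2, Day 8 | Baseline, Day 8 (Tables 14.3.4.1, 14.3.4.2) | Day 2 |
| Fibrinogen | Screening, Day 2, Day 8 | all three (SAP 9.2.4; Tables 14.2.4.1 to 14.2.4.3) | none |

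For antibodies and for TT, PT and aPTT alike, 1 of 3 time points, and 1 of 2 after baseline, has no by-visit summary.

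**Step 2: where the antibody table stops.** The last scheduled injection is on Day 6.
- Day 8 sample: 8 − 6 = 2 days later.
- Day 30 sample: 30 − 6 = 24 days later.
- With the visit windows in SAP 4.3 (Visit 4 on Day 6 or 7; Visit 5 on Day 7 to 9, on a different day from Visit 4; Visit 6 on Day 23 to 37), the Day 8 sample falls 1 to 9 − 6 = 3 days after the last injection. The Day 30 sample falls 23 − 7 = 16 to 37 − 6 = 31 days after it.
- In a patient whose injections stop after Day 2, the nominal gaps are 8 − 2 = 6 and 30 − 2 = 28 days.

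For patients given the full course, Day 30 is therefore the only sample more than a few days after the last injection.

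**Step 3: whether another planned output fills the gap.**
- Table 14.3.4.4 could include a Day 2 or Day 30 value, but it is by parameter, not by visit, and SAP 10.3 does not define clinical relevance. It gives no rate at either visit. Post-dose coagulation results are in principle withheld from the investigator (Protocol 3.1), so an investigator's judgement of relevance is not normally available for them.
- The adverse event tables are no substitute for the Day 2 values. Protocol 9.1.1 excludes fibrinogen, TT, PT and aPTT from the abnormal laboratory values it gives as examples of adverse events.
- SAP 13.7 says no table shells will be made, and SAP 13.6 offers in-text tables on request only. The wording of SAP 10.3 therefore decides what is programmed.

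**Step 4: the duplicate rule, case by case.**
- Local value in the CRF and a central value with its range: the rule selects the local value, which has no range and cannot be placed in the shift table.
- CRF copy of a central value: possible, because SAP section 2 records that central-laboratory parameters were added to the CRF with Amendment 4.1. The SAP does not say whether the copy keeps its range.
- Only one source: the rule does not apply.

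The loss is certain only in the first case. The documents give no count of such pairs.

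**The case against.** The strongest reply is that little is lost. Every result is listed, including both members of a duplicate pair, with separate listings for coagulation and antibodies sorted by treatment, patient and visit. SAP section 2 expects only a few more evaluable patients than the 30 planned for the interim look. At 2:1, 30 patients would be about 20 on ancrod and 10 on placebo, and antibody status can be counted from a listing of that size. SAP 4.6 promises descriptive analysis of all study variables, so the two-visit parenthesis may be a slip. Protocol 2.4.1 ties neutralizing antibodies to a second course and to long-term subcutaneous use, which this one-week regimen is not. Day 2 fibrinogen, which governs the Day 4 and Day 6 injections, is tabulated.

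Most of this stands and limits the size of the point. It does not remove it: a general promise of description does not override a specific rule naming two visits, and a listing is not a planned comparison by arm.

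Four stronger readings are tempting, and the documents do not support them.
- A reader might infer that these data are thrown away or missing from every table. They are listed, and Table 14.3.4.4 has no visit limit.
- A reader might infer that the most informative safety data are lost. That is a judgement. Adverse event tables and Day 2 fibrinogen remain.
- A reader might infer that all duplicate values fall out of the shift table. SAP 4.3 says only that local values entered in the CRF lack ranges.
- A reader might infer that the same CRF-first rule in SAP 9.2.4 puts a between-laboratory offset into the fibrinogen change. Where follow-up is local, the laboratories match. Where follow-up exists only centrally, the rule is not triggered, and any mixing comes from the protocol's local screening assay. Randomization is blocked within center and center is in the model, so a constant site offset would largely cancel. SAP 4.2 also refers to SAP 4.3 for baseline fibrinogen, and part of SAP 4.3 was not in the text available here.

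**Conclusion.** The point holds as a gap in reporting. SAP 10.3 conflicts with SAP 3.4.3 and with the sampling schedule, so Day 30 antibodies and Day 2 TT, PT and aPTT have no planned by-visit summary by arm. That the Day 2 and Day 30 omissions are real rests on the text alone. That Day 30 is the only late antibody sample assumes the full course of injections.

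The duplicate rule is a conditional weakness: it costs a classification only where a local CRF value sits beside a central value with a range, and its frequency cannot be determined from the documents. Nothing here bears on the primary analysis, alpha, power or sample size, and no result is removed from the listings.

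**What to change.** Amend SAP 10.3 before unblinding:

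1. Add Day 30 to the antibody frequency table: positive and negative by arm, plus the number newly positive since Screening. SAP 4.6 limits by-visit tables to patients who have not yet terminated, so state that Day 30 samples from early terminators, which Protocol 4.5 asks for, are included.
2. Add Day 2 to the TT, PT and aPTT summary table.
3. For the shift table only, classify by the central value and its range where one exists. Where both sources are available, keep each change from baseline within one laboratory.

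A blanket switch from CRF to central values is not advised. Screening coagulation is assayed locally, so where Day 8 TT, PT or aPTT exists in both sources, the switch could turn a local-to-local change into a local-to-central one.

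The cost is a few sentences and some programming, with no new samples or data. The shift table may then rest on a different value from the summary table, which needs a footnote.

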## 2.4 Potential Risks and Benefits

### 2.4.1 Potential Risks

Due to its mode of action, bleeding may occur during ancrod treatment. The direct effect of ancrod on the coagulation cascade and on platelet function may cause microscopic hematuria, bleeding at puncture sites, bruising and, in rare cases, melena, epistaxis, and hematemesis (Latallo, 1983). Many bleeding adverse events are related to bruising and are of limited clinical significance. The

|                                |                             |                      |
|--------------------------------|-----------------------------|----------------------|
| Protocol Amendment 7.1         | Study no.: NM-V-101         | Page 23 of 85 |
| Date of Amendment: 15 Feb 2018 | EudraCT No.: 2012-000066-37 |                      |

bleeding risk appears to be increased when fibrinogen levels remained below 40 mg/dL for longer periods.

The relatively high incidence of adverse events observed in clinical studies in patients with acute ischemic stroke treated with ancrod may be attributed to advanced age, predisposition, and vulnerability of this patient population and cannot be extrapolated to patients with sudden hearing loss who will be treated with a different, moderate dosing regimen. Further, the incidence of adverse events observed in the direct comparison of defibrinogenation therapy with corticosteroid revealed no minor or major bleeding. Side effects were observed in 84.9% of patients who received defibrinogenation therapy and in 85.9% of patients who received corticosteroid treatment (Kubo et al., 1988).

Local reactions, such as urticaria and exanthema, are rare but may occur after subcutaneous use. Some patients who had received ancrod subcutaneously developed local irritation or itching. These skin reactions have responded to antihistamine therapy. There was no evidence of an allergic reaction in healthy subjects or in patients treated with ancrod repeatedly. Nevertheless, special attention should be paid to patients receiving a second course of ancrod because neutralizing antibodies may occur particularly after long-term subcutaneous administration.

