## Urinalysis

At screening and on day 8: Hemoglobin or blood in urine, pH, specific gravity, protein, glucose, ketones, bilirubin, and leucocytes.

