#### **10.6. Otolaryngological Examination**

An otolaryngological examination is performed at Screening (Visit 1), Day 8 (Visit 5), Day 30 (Visit 6), and Day 90 (Visit 7). While the assessments to estimate hearing loss are evaluated for efficacy, the following items collected at Screening and Day 8 represent safety parameters:

- Ear microscopy results (affected ear)
- Tympanometry results (affected ear)
- Stapedius reflex measurements results (affected ear)
- Otoacoustic emissions examination results (affected ear)

Separately for each item, the categories 'Normal' and 'Finding' will be given in a frequency table by visit. Any specifications on findings will be presented in a patient data listing.

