#### **10.7. Vital Signs**

Vital sign parameters (body weight, systolic and diastolic blood pressure, and pulse rate) are recorded for Screening (Visit 1) and Day 8 (Visit 5). All data will be listed. Values of above four parameters for Screening and Day 8 and the absolute change from Screening to Day 8 will be displayed in a summary table.

In addition, a frequency table will be provided for pulse pattern ('Regular', 'Not regular') by visit.

Vital signs will also be tabulated in shift tables providing the number of patients whose values are within or outside the normal ranges. The following normal ranges (orientating at WHO definitions) will be used:

- BMI: 18.5 to <25.0 kg/m^2
- Systolic blood pressure: 105 to <140 mmHg
- Diastolic blood pressure: 65 to <90 mmHg
- Pulse rate: 60 to <85 beats per minute.

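### Blood in urine and ear findings are defined as change variables but tabulated as separate per-visit counts, which do not give the number of new-onset cases

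*Combined protocol and SAP*

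**What the plan says.** Protocol 2.4.1 says that ancrod's action on coagulation and platelets "may cause microscopic hematuria, bleeding at puncture sites, bruising" and, rarely, more serious bleeding. Protocol 8.2.2 schedules the urine test twice ("At screening and on day 8: Hemoglobin or blood in urine") and says that laboratory safety is assessed on changes. SAP 3.4.3 agrees: it lists change in laboratory parameters and "Change from Screening to Day 8 in otolaryngological examination findings".

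The tabulation rules differ by type of parameter. In SAP 10.3, "a shift analysis will be presented for each numeric parameter", running from Baseline to Day 8 in three categories (below, within and above the normal range). Table 2 of the SAP marks blood in urine as positive/negative, and for that type "Categorical parameters will be presented in frequency tables by visit (Baseline, Day 8". In SAP 10.6 the normal/finding counts for ear microscopy, tympanometry, stapedius reflex and otoacoustic emissions "will be given in a frequency table by visit". The table list matches: 14.3.4.2 is a shift analysis of numeric laboratory values, while 14.3.4.3 (categorical laboratory values) and 14.3.6 (ear examination) carry no shift in their titles. For vital signs, SAP 10.7 plans shift tables "providing the number of patients whose values are within or outside the normal ranges".

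**The concern.** A change variable is a statement about each patient: negative before and positive after, or the reverse. Two separate frequencies give only the net movement in the arm, so one new case and one case that clears leave the count unchanged. Blood in urine is the first effect named in the protocol's bleeding-risk text, and it is a scheduled test that does not depend on spontaneous reporting. The natural safety question is how many patients without blood in urine at baseline had it on Day 8, by arm. The planned table does not answer it, although paired values are scheduled. The SAP does record individual change elsewhere, in the numeric shift table and in the change/no change coding of the Day 8 physical examination (SAP 10.5).

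**Working it through.** **Inputs.** The plan gives no rate for blood in urine at any visit, so there is no plan figure to reproduce on this point. The denominators come from SAP 3.5: 66 ancrod and 33 placebo. That calculation holds together: 29 + 58 = 87 evaluable patients, and 87/(1 − 0.12) = 98.9, rounded up to 99, using the 12% dropout in SAP 5.3. SAP section 2 expects only a few more than 30 evaluable patients, so I also use 20 and 10, which is 30 split 2:1.

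**What per-visit counts identify.** Let b of N patients be positive at Baseline and d at Day 8. The number newly positive lies between max(0, d − b) and min(d, N − b).

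| N (ancrod) | Baseline | Day 8 | New-onset cases possible |
|---|---|---|---|
| 66 | 3 | 3 | 0 to 3 |
| 66 | 7 | 7 | 0 to 7 |
| 66 | 13 | 13 | 0 to 13 |
| 66 | 7 | 10 | 3 to 10 |
| 20 | 4 | 4 | 0 to 4 |

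**What the Day 8 contrast between arms still shows.** Assume a baseline positive rate p0 equal in both arms, half of the positives clearing in each arm, and new onset among baseline negatives of 25% on ancrod and 5% on placebo. The Day 8 rate is 0.5·p0 + (1 − p0)·(new-onset rate).

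| p0 | Ancrod Day 8 | Placebo Day 8 | Difference (points) |
|---|---|---|---|
| 10% | 27.5% | 9.5% | 18 |
| 20% | 30% | 14% | 16 |
| 30% | 32.5% | 18.5% | 14 |

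With equal clearance the difference is (1 − p0) × 20 points, whatever the clearance rate is. The 20-point difference among patients at risk is diluted but remains visible.

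**When the contrast can mislead.** It needs unequal baseline rates, or clearance that differs by arm.

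- *Chance imbalance.* At p0 = 20% with 20 and 10 patients, the standard deviation of the baseline difference between arms is √[0.2 × 0.8 × (1/20 + 1/10)] = 0.155, or about 15 points. One placebo patient alone moves that arm by 10 points.
- *An extreme case at planned size (assumed).* On ancrod, 7 of 66 are positive at baseline, all 7 clear and 7 others become positive. On placebo, 3 of 33 are positive, all 3 persist and none is new. Day 8 status is 7/66 against 3/33 (Fisher p = 1.00). New onset is 7/59 (11.9%) against 0/30 (p = 0.09).
- *The same pattern at the expected size.* Day 8 status is 4/20 against 2/10 (p = 1.00), and new onset is 4/16 against 0/8 (p = 0.26).

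The last two cases were chosen to show the limit of what can happen, not what is likely.

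**The case against.** The strongest reply is that safety tables are shown by treatment group, so randomization protects the Day 8 comparison. That stands: under equal clearance the planned table shows 30% against 14%. A reader might infer that new haematuria is masked, or might quote the ancrod arm alone (from 30% at baseline to 32.5%, a net 2.5 points) as if the signal had vanished. The documents do not support this, because on the same assumptions placebo falls from 30% to 18.5% and the arms differ by 14 points.

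The second reply is that the per-visit table is not the only output. This also stands, in part:

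- SAP 10.3 adds a count of patients with clinically relevant laboratory values by parameter (Table 14.3.4.4), but states no visit or baseline reference for it.
- Protocol 9.1.1 makes an abnormal laboratory value an adverse event if the investigator judges it clinically significant, and protocol 9.1.7 does not count conditions present at screening unless they worsen. Significant new haematuria should therefore reach the adverse event tables, but through judgement.
- Protocol 10.2.2 plans a summary of bleeding events. The SAP's table list shows no separate one.
- Listings 16.2.8.4 and 16.2.6.3 hold the paired values, and with about 30 patients a reader could count by hand. No information is lost; it is left untabulated.

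Two further limits apply. The urine test is scheduled at both visits, which does not show that every patient has both results; SAP section 2 warns that values will be missing for parameters added to later CRF versions. And a reader might take the vital-sign wording in SAP 10.7 to mean that a move from high to low counts as no change. The wording is loose and does not settle the layout, and the same section also plans values at both visits and absolute changes.

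**Conclusion.** The point holds as a reporting gap. The SAP defines these safety variables as changes, then tabulates the categorical ones as status at each visit, and status counts do not determine new onset. For an unchanged count of 7 in 66, the uncertainty is the full range from 0 to 7; for 4 in 20, it is 0 to 4. That result is arithmetic and needs no assumption about rates. How far the Day 8 contrast is diluted does depend on assumed rates: a 20-point difference among patients at risk becomes 14 to 18 points for baseline positivity of 30% down to 10%. Distortion beyond dilution requires chance imbalance, which is plausible at about 20 and 10 patients, or clearance that differs by arm, for which the documents give no evidence. The primary endpoint is not affected. The documents name no specific clinical concern behind the ear findings, so the argument there rests on consistency with SAP 3.4.3.

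**What to change.** In Tables 14.3.4.3 and 14.3.6, add a Baseline by Day 8 cross-tabulation per arm (negative/positive for categorical laboratory parameters, normal/finding for the four ear items). Report new positives or new findings as n/N among patients negative or normal at baseline, and show missing pairs. Keep it descriptive, in line with SAP section 10. An exact interval for blood in urine is optional and will be wide: 4/16 has a 95% Clopper-Pearson interval of 7% to 52%, and 0/8 one of 0% to 37%.

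In SAP 10.7, state that the vital-sign shift tables (Table 14.3.7.3) use below, within and above the normal range, as SAP 10.3 does for laboratory values.

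SAP 13.7 says that no table shells will be produced, so the layout should be written into the SAP text or its addendum before unblinding. The cost is slightly more table output. No new data and no change to study conduct are needed.
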